### Population

Adult patients (≥18 years) who were for the first time diagnosed with hyperthyroidism (the list of codes in online supplemental appendix) between 1 January 1996 and 31 December 2015 will be eligible for inclusion. To minimise missed cases, the diagnosis will be additionally identified by a prescription of carbimazole or propylthiouracil, which are ATDs indicated only for treatment of hyperthyroidism. A minimum of 12 months of data must be available before the date of diagnosis and after the index date. CPRD records need to be classified as acceptable research quality.

10.1136/bmjopen-2021-055219.supp1Supplementary data

Exclusion criteria encompass ATD treatment of duration shorter than 6 months as the only treatment, that is, with no radioactive iodine or thyroidectomy followed. This is to avoid contamination by misdiagnosis or spontaneously resolving thyroiditis. Patients treated with both definitive treatment methods, that is, radioiodine and thyroidectomy, will also be excluded. However, ATD treatment followed by either radioiodine or thyroidectomy (one of the definitive treatments) is considered a pretreatment and does not constitute an exclusion criterion.

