### Index date and follow-up

The index date in the cohort is the date of initiation of treatment for hyperthyroidism, which defines the treatment group (either ATD, radioiodine or thyroidectomy). There is a requirement of at least 12 months’ data available prior to the index date.

The natural history of weight changes will be modelled preindex and postindex date. While the follow-up for the analysis of outcomes will start at the index date, a minimum of 12-month follow-up is required for the inclusion.

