The estimation of propensity weights will be conducted by the method proposed by McCaffrey *et al*.^31 32^ The appropriateness of IPW analysis will be assessed by checking the overlap (positivity assumption). According to the positivity assumption, each patient should have a non-zero probability of being indicated to each treatment category. Lack of overlap in the distribution of observed pretreatment characteristics between groups receiving different treatment indicates the positivity assumption is violated. This overlap will be checked visually. If poor overlap is identified, we will use Rubin’s trimming method,^33^ allowing discarding non-overlapping cases.

Further, pairwise balance in the distribution of all included variables between the three treatment groups will be tested with linear regression for continuous variables, logistic regression for binary and multinomial logistic regression for nominal variables. The analysis will be done without and with adjustments. The propensity weights will be considered balanced if there are no statistically significant (p<0.05) differences between the likelihood of receiving a different type of treatment. If imbalances remain after weighting, a doubly robust estimation approach will be applied^32^; that is, the imbalanced variables will be added to the model.

While IPW will adjust for confounding at baseline, other time-varying adjustments will be applied to correct for the events between the baseline and the outcome. The proposed covariates are treatment with levothyroxine for developed hypothyroidism, log TSH levels and informative observations of number of GP visits in a unit of time.

Incidence rate ratios of outcomes will be calculated with Poisson regression and modelled adjusting for time-varying covariates as listed further. Time-to-event analysis with adjustments will be modelled. The appropriate model will be applied, depending on the proportional hazard assumption’s results: if the assumption holds—Cox proportional hazard regression will be used; if it is violated, alternative techniques such as time-varying measures in extended Cox models will be applied.

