#### Sensitivity to missed radioiodine record

Whenever ATD patients develop permanent hypothyroidism, a radioiodine treatment will be assumed, as explained in the Exposure section. All analyses will be repeated to check sensitivity to this assumption, excluding patients in the ATD group who developed hypothyroidism following medical treatment being the only antithyroid treatment on record.

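### Excluding anyone who receives both radioiodine and thyroidectomy makes eligibility depend on an event after the index date, with a bias of unknown size and direction

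*Protocol article*

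**What the plan says.** The Population section removes one group without qualification: "Patients treated with both definitive treatment methods, that is, radioiodine and thyroidectomy, will also be excluded". It gives no time window, no order of procedures and no reason; a reason is given only for the neighbouring exclusion of short ATD courses. The same section restricts the cohort to adults "who were for the first time diagnosed with hyperthyroidism" in the study period. It treats the other kind of switch differently: "ATD treatment followed by either radioiodine or thyroidectomy (one of the definitive treatments) is considered a pretreatment and does not constitute an exclusion criterion".

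The Index date and follow-up section says: "The index date in the cohort is the date of initiation of treatment for hyperthyroidism, which defines the treatment group". It adds that "the follow-up for the analysis of outcomes will start at the index date".

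The Exposure section defines the medical arm by ATD treatment longer than six months with no code for either definitive procedure.

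**The concern.** Whether a patient will go on to a second definitive procedure is not known at the index date. A rule that uses this information selects on the future. Take a hypothetical patient given radioiodine in 2000 and surgery in 2014. The patient contributes nothing, although 2014 − 2000 = 14 years of follow-up had already accrued under the first treatment, together with any weight records and events in that time.

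At stake is whether each definitive arm describes what follows from choosing that treatment. The Introduction and the Patient and public involvement section say patients want the results to inform that choice. At the point of choice nobody knows whether a second procedure will follow. The removed patients are also unlikely to be a random subset. The Introduction reports weight gain after radioiodine of 7.1 kg with later hypothyroidism and 5.1 kg without, so thyroid response to the first procedure is related to the primary outcome, and a second procedure plausibly depends on that response.

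**Working it through.** The protocol gives no figure for this exclusion, so there is none to reproduce. The check is first one of timing, then an illustration with assumed inputs.

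**1. Timing.** Entry is at first diagnosis, so the first definitive procedure should normally lie in the observed record. The natural reading is that this procedure defines the group and sets the index date. The second then falls after the index date, inside follow-up. The exclusion therefore acts on post-index information.

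**2. Does anything in the plan repair it?** The Cardiometabolic risks and mortality section says: "While IPW will adjust for confounding at baseline, other time-varying adjustments will be applied to correct for the events between the baseline and the outcome". Baseline weights balance the patients who remain; they do not bring back those removed. The same holds for the time-varying terms (levothyroxine, log TSH, GP visits). The planned sensitivity checks concern death and missed treatment coding. The one set out in detail addresses the radioiodine proxy: "All analyses will be repeated to check sensitivity to this assumption, excluding patients in the ATD group who developed hypothyroidism". None varies the rule on both procedures.

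**3. Illustration without survival.** Let f be the share of an arm that switches and RR the event rate of switchers relative to the others (both assumed). Then

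retained-arm rate / whole-arm rate = 1 / [(1 − f) + f × RR].

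- f = 0.01, RR = 1.5: 1 / (0.99 + 0.015) = 0.995
- f = 0.05, RR = 2: 1 / (0.95 + 0.10) = 0.952
- f = 0.10, RR = 2: 1 / (0.90 + 0.20) = 0.909
- f = 0.10, RR = 3: 1 / (0.90 + 0.30) = 0.833

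This formula moves in one direction only, because it ignores that a switcher must live to the second procedure.

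**4. Illustration with survival.** A simulation assumed constant mortality of 0.02 per year, 10 years of follow-up and a second procedure at a time uniform between 0.5 and 3 years. Only those alive at that time were excluded. The ratio of retained to whole mortality rate was:

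| Share who would switch | RR 1 | RR 1.5 | RR 2 | RR 3 |
|---|---|---|---|---|
| 1% | 1.002 | 0.998 | 0.995 | 0.989 |
| 3% | 1.005 | 0.995 | 0.984 | 0.968 |
| 5% | 1.010 | 0.991 | 0.974 | 0.949 |
| 10% | 1.021 | 0.983 | 0.952 | 0.906 |

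At RR = 1 the ratio exceeds 1: would-be switchers who die early stay in, while those who survive to switch are removed with their event-free time. The simulation does not apply the protocol's 12-month minimum follow-up, which would shrink this survival component.

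**5. Weight.** If switchers differ from the others by d kg, the retained mean differs from the whole mean by −f × d. With d = ±2 kg (assumed; the same size as 7.1 − 5.1), the shift is 0.02 kg at f = 0.01 and 0.20 kg at f = 0.10, in either direction.

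**The case against.** The strongest reply is that the rule gives a clean comparison of single treatments, touches few patients and has no demonstrable direction. Much of this stands.

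- **A reader might infer that the definitive arms are cleared of failures.** The sentence removes only patients who had both radioiodine and thyroidectomy. Those re-treated with the same method, or returned to ATDs, stay. The protocol does not say why patients receive both, so failure of the first procedure is itself an inference.
- **A reader might infer that the definitive arms will look better than they are.** Required survival to the second procedure pushes mortality the other way. For weight, if switchers resemble radioiodine patients who did not become hypothyroid (5.1 kg against 7.1 kg), removing them could make radioiodine look worse.
- **A reader might infer a bias against ATD.** ATD patients who go on to a definitive procedure leave the medical arm by definition. The Introduction puts ATD relapse at 30% to 70%; the share of relapsers who switch is not given. All three arms are selected in some degree on not moving to a further treatment, so a calculation on the definitive arms alone cannot support a between-arm direction.
- **Keeping these patients is not free.** It interacts with the treatment-phase definition in the weight model, and censoring at a second procedure is informative.

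What does not stand is the defence of the rule itself. Interest in single-treatment effects is legitimate, but it can be met by weighted censoring at the second procedure without deleting the patient from the start.

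**Conclusion.** The design fault is established from the text: an exclusion with no time limit is combined with follow-up from the group-defining treatment, so eligibility rests on a post-index event, and nothing listed corrects it. That the exclusion covers the whole later record is the plain reading of a sentence that sets no limit.

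Size and direction are not established. Under the assumed inputs of the simulation, the effect on one arm's mortality rate is about −1% to 0% at a 1% switch share and −9% to +2% at 10%. The weight shift is at most 0.20 kg either way if switchers differ by 2 kg. Switch share, rate ratio, mortality and timing are all assumptions, and none comes from the protocol. The point merits a change to the plan because the rule is avoidable; it does not show that the results would be materially wrong.

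**What to change.** Replace the exclusion with a rule that assigns these patients to the arm of their first definitive treatment, from its index date. Then:

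1. Analyse the outcomes with follow-up continued after the second procedure, and again with censoring at it. Use inverse probability of censoring weights in the second analysis, because that censoring is informative.
2. In the weight model, end or censor the phases at the second procedure. The Natural history of weight changes section runs the treatment phase to three months past the latest treatment on record. Unchanged, that rule would turn the 2000 and 2014 example into a treatment phase of more than 14 years.
3. Report the number affected in each arm. The count is likely to be too low, since the Exposure section expects many radioiodine records to be missed.
4. Keep the exclusion as now written as a sensitivity analysis.

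No new data are needed: the procedure records must already be identified in order to exclude these patients. The cost is some person-time after a second procedure in one analysis and modest extra analysis work. The change does not alter how the ATD arm is defined, so selection on never switching remains there and should be acknowledged when definitive arms are compared with ATD.

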### Exposure

The exposure in the study is the treatment for hyperthyroidism. The study patients will be divided into three groups based on the treatment administered: (1) radioiodine: the allocation to this treatment arm will be assigned based on the Read code or OPCS-4 code of the treatment procedure for radioiodine; (2) thyroidectomy: the allocation to this treatment arm will be assigned based on the Read code or OPCS-4 code of the surgical procedure; (3) medical treatment arm will be identified based on the absence of radioiodine treatment code and thyroidectomy code in the presence of ATD treatment (based on the Read code or British National Formulary (BNF) code) longer than 6 months.

We anticipate good quality of ATD prescription and thyroidectomy. However, radioiodine, typically administered in outpatients, may be missed in a substantially high proportion of patients. Since ATD treatment does not incur permanent hypothyroidism, the long-term prescription of levothyroxine for hypothyroidism following treatment with ATD alone, that is, without any definitive procedures, will be considered as a proxy for radioiodine administration.

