## Introduction

Hyperthyroidism is a common condition affecting 3% of women and 0.3% of men in the UK.^1^ Common clinical features indicating hyperthyroidism include weight loss, heat intolerance, tremor, palpitations and anxiety.^2^ Treatment is critical to minimise complications including atrial fibrillation and stroke that contribute to the observed 20% increase in mortality.^3^

There are three treatment options: antithyroid drugs (ATDs), radioactive iodine (I-131, radioiodine) or surgical, either as a total or hemithyroidectomy. ATDs are associated with a high rate of relapse (30%–70%),^4^ while treatment with radioiodine or thyroidectomy leads to the development of hypothyroidism, requiring lifelong levothyroxine replacement, which is seen in 80% of patients administered radioiodine and up to 100% undergoing thyroidectomy. Guidance recommends discussion of all three options with the patient.^5 6^ There is insufficient evidence to recommend one treatment over the others, although some studies indicate differences in cardiac events and mortality between the treatment modalities.^7 8^

Weight gain following various treatments for hyperthyroidism has been described.^9 10^ Clinicians commonly assume that the observed weight gain is a simple regain of weight lost prior to the initiation of treatment. However, an analysis of 1373 patients with hyperthyroidism has demonstrated a higher prevalence of obesity at 3 years of follow-up when compared with the age-matched and sex-matched background population (37% vs 26% in men, p<0.001; 32% vs 26% in women, p<0.001).^11^ These findings suggest excess weight gain beyond patients’ premorbid weight (weight overshoot). Additionally, the study showed significant differences in final weight gain compared with baseline between those treated with ATDs (5.4 kg, 95% CI 4.8 to 6.0) and those who received radioiodine but did not develop hypothyroidism (5.1 kg, 95% CI 4.3 to 6.1) when compared with those treated with radioiodine who developed subsequent hypothyroidism (7.1 kg, 95% CI 6.6 to 7.7). The extent of weight change in patients treated with thyroidectomy was not evaluated.

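### The check on the levothyroxine proxy for missed radioiodine removes the same patients from the ATD arm as the main analysis does, so the premise behind the proxy is never tested

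*Protocol article*

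**What the plan says.** The Exposure section of the protocol article first defines the medical arm by ATD treatment longer than 6 months with no radioiodine or thyroidectomy code. It then concedes that "radioiodine, typically administered in outpatients, may be missed in a substantially high proportion of patients". To recover the missed cases it reasons "Since ATD treatment does not incur permanent hypothyroidism" and concludes that "the long-term prescription of levothyroxine for hypothyroidism following treatment with ATD alone, that is, without any definitive procedures, will be considered as a proxy" (of radioiodine).

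The section on sensitivity to missed radioiodine records restates the rule without exception: "Whenever ATD patients develop permanent hypothyroidism, a radioiodine treatment will be assumed". It presents its repeat of all analyses as a test of that assumption, and the repeat is done by "excluding patients in the ATD group who developed hypothyroidism following medical treatment being the only antithyroid treatment on record".

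The section on the natural history of weight changes makes ATD the reference group and also promises a check on missed treatment codes, but gives no other rule. Table 2 defines levothyroxine replacement for the radioiodine and thyroidectomy groups only. The Introduction says that hypothyroidism needing lifelong levothyroxine follows both definitive treatments, "which is seen in 80% of patients administered radioiodine and up to 100% undergoing thyroidectomy".

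**The concern.** Exposure is assigned partly from something that happens after treatment. The Introduction links that same event to the primary outcome: in the earlier cohort it cites, mean gain after radioiodine was 7.1 kg with subsequent hypothyroidism and 5.1 kg without. A rule that sorts patients by hypothyroidism can therefore shift the weight comparison, and because ATD is the reference group, it affects both contrasts with ATD. The same classification carries into the cardiometabolic and mortality analyses.

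A sensitivity analysis for such a rule should show what happens if the rule is wrong. Here the rule is wrong if some reassigned patients had ATD alone and became hypothyroid. Neither analysis puts any of them back in the ATD arm. Agreement between the two could be taken as support for the premise when the premise has not been varied on the ATD side.

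**Working it through.** **1. Who is in each arm.** This step needs no assumed rates.

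| Patients | Main analysis | Planned check | As recorded |
|---|---|---|---|
| ATD only, no levothyroxine | ATD | ATD | ATD |
| ATD only, long-term levothyroxine | radioiodine | excluded | ATD |
| Radioiodine uncoded, hypothyroid | radioiodine | excluded | ATD |
| Radioiodine uncoded, euthyroid | ATD | ATD | ATD |
| Radioiodine coded | radioiodine | radioiodine | radioiodine |

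Rows 2 and 3 look identical in the data. The ATD column has the same membership in both planned analyses. No third analysis is stated.

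**2. The proxy works in one direction.** On the Introduction's 80% figure, it catches 80% of uncoded radioiodine patients and leaves 20% in the ATD arm. Take 2,000 true radioiodine patients with 40% uncoded, and suppose the premise holds. The arm becomes 1,200 coded (960 hypothyroid) + 640 proxy = 1,840, of whom 1,600 are hypothyroid: 87.0% instead of 80%.

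**3. Illustrative size, crude arm means.** The article states no figure to reproduce. From the Introduction: 7.1 kg with hypothyroidism, 5.1 kg without, 80% hypothyroid after radioiodine. Assumed: gain depends only on hypothyroidism; 5,000 true ATD and 2,000 true radioiodine patients; 40% of radioiodine uncoded; 10% of true ATD patients become hypothyroid.

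- Truth: radioiodine 0.8 × 7.1 + 0.2 × 5.1 = 6.70; ATD 5.1 + 0.10 × 2.0 = 5.30; difference **1.40 kg**.
- Main analysis: radioiodine 1,200 + 640 + 500 = 2,340, of whom 2,100 (89.7%) are hypothyroid, mean 6.89; ATD 5.10; difference **1.79 kg**. Of the 1,140 reassigned patients, 500 (44%) truly had ATD alone.
- Planned check: 6.70 − 5.10 = **1.60 kg**.
- As recorded: ATD arm 5,800, of whom 1,140 are hypothyroid, mean 5.49; 6.70 − 5.49 = **1.21 kg**.

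**4. Range, with the protocol's own premise included.** The ranges cover 20% to 60% of radioiodine uncoded.

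| True ATD hypothyroid | Truth | Main | Planned check | As recorded |
|---|---|---|---|---|
| 0% (the premise) | 1.60 | 1.67–1.82 | 1.60 | 1.29–1.48 |
| 2% | 1.56 | 1.68–1.83 | 1.60 | 1.26–1.44 |
| 10% | 1.40 | 1.74–1.86 | 1.60 | 1.13–1.30 |
| 20% | 1.20 | 1.78–1.88 | 1.60 | 0.97–1.11 |

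**5. Second model.** This one uses 5.4 kg, the Introduction's ATD mean, for ATD patients without levothyroxine. It varies the ATD:radioiodine ratio (1:1, 2:1, 4:1), the uncoded share (10%, 30%, 50%), the ATD hypothyroid share (0%, 5%, 10%, 20%) and the extra gain in hypothyroid ATD patients (0, 1, 1.7, 2 kg), giving 117 distinct scenarios. The two planned results enclose the truth in 23, all with some ATD hypothyroidism and no extra gain. With the as-recorded result added, the set encloses it in all 117. Wherever some true ATD patients become hypothyroid and gain at least 1 kg extra, both planned results exceed the truth. Example (2:1, 30%, 10%, 1.7 kg): truth 1.13, main 1.46, check 1.31, as recorded 0.98.

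**The case against.** The strongest reply is that the kilogram figures are not the bias of the planned estimate. They are differences in crude means, while the Confounding section adjusts for levothyroxine replacement and thyroid function. If gain depended only on hypothyroidism, a model that conditions on it would give a contrast near zero under any classification. This stands as regards size. It does not answer the structural point: adjustment cannot return hypothyroid patients to an arm that has none by construction.

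Second, the documents give no rate of permanent hypothyroidism after ATD alone, and the protocol says it does not occur. At 0% the planned check is unbiased in the first model (1.60 against 1.60) and nearly so in the second (1.31 against 1.30 at 2:1 with 30% uncoded). The check also has a use, since it shows how far the reassigned patients drive the radioiodine arm. Both points stand.

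A reader might infer that both planned analyses always overstate the difference, or can never enclose the truth. The 0% row and the 23 scenarios show that this goes too far. A reader might also infer that recorded procedures should be the primary classification. The numbers do not support that: in the base case the as-recorded result errs by −0.19 kg and the planned check by +0.20 kg, as-recorded does worse at lower ATD hypothyroidism, and the authors expect heavy under-coding.

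Finally, a reader might infer that the plan contains immortal time. The index date is the start of the treatment that defines the group, and proxy cases have no recorded radioiodine date. But the article does not say how they are dated, and the full protocol may. That is a point to check, not an error shown.

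**Conclusion.** The point holds in its structural form, and that part depends on no assumed rate. The stated check cannot show what happens if the reassigned patients truly had ATD alone, because it leaves the ATD reference arm unchanged. The proxy also enriches the radioiodine arm for hypothyroidism even when the premise is true.

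The direction of error is conditional. If some true ATD patients become hypothyroid and gain more weight as a result, both planned analyses overstate the crude radioiodine-minus-ATD difference: by 0.39 and 0.20 kg in the base case. Those values rest on assumed rates, an assumed arm ratio and no covariate adjustment, so they are not estimates of the bias in the planned models. The authors disclose the coding gap and state their assumption openly. What is missing is the second bound. This should be fixed before analysis, but it does not invalidate the design.

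**What to change.** Keep the proxy analysis and the exclusion analysis. Add to the section on missed radioiodine records a second sensitivity analysis in which patients with only ATD on record stay in the ATD arm whether or not they later take levothyroxine. For that run, extend the Table 2 definition of levothyroxine replacement to the ATD group; otherwise the covariate is undefined for the patients in question. Report the proxy, exclusion and as-recorded results side by side, and state how many radioiodine patients are there by proxy only.

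Separately, state the index date used for proxy cases, and check that it does not credit radioiodine with follow-up that a patient had to survive in order to be classified.

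The cost is one more run of each analysis and a few sentences of text. No new data are needed.
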